## Methods

The guided text-based intervention for people who suffer from PGD after bereavement due to haematological cancer is currently evaluated in a randomized waitlist-controlled trial. Questionnaires are administered at screening for eligibility (T-1), at baseline (T0), during the intervention (monitoring), at post-treatment (T1) and at three follow-up points (T2–4; 3, 6, and 12 months after intervention completion). Severity of PGD symptoms as measured with the Inventory of Complicated Grief (ICG) [48] is the main outcome. All questionnaires and the intervention are administered via a secure website and data is stored on secure storage devices. The procedure is described in detail below.

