### Procedure

#### Recruitment practices

Short information about the study and a link to the study website is sent to a multitude of stakeholders, including support groups, charities, insurance companies, clinics and medical practices, owners or contact persons of relevant websites, online communities, and blogs in Germany. Flyers are sent via mail by request and distributed in departments of the University Medical Centre Leipzig, e.g., Psychosomatic Medicine, Medical Psychology and Medical Sociology, and Haematology and Medical Oncology.

The study website provides thorough information about the study and the Internet-based grief therapy. Interested persons can apply by submitting a screening questionnaire which determines whether they fulfil eligibility criteria. Contact information of the research team is provided to be addressed in case of questions and remarks.

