**Fig. 1 Fig1:**
[figure not shown]
Participant timeline

*T-1, screening:* Participants apply for the study via an openly accessible online questionnaire. Participants who may fulfil the eligibility criteria as described below will be contacted for a telephone screening, which includes the Prolonged Grief Interview [7, 49] and in case of eligibility concerns queries regarding participant’s answers in the online questionnaire. Participants who do not fulfil the eligibility criteria but show signs of suicidal ideation will also be called to ensure their safety and provide support in finding immediate help if necessary. Participants who are excluded from the study after the screening process will receive information about the reasons via e-mail and be offered help in finding an alternative treatment.

*Informed consent:* Participants meeting the eligibility criteria will be sent thorough information on the study and asked to send back a consent form, which also includes contact information of the participant’s general practitioner, who will be contacted in case of endangerment to self or others. Participants are informed about this requirement. Questions can be addressed to the research team at any time.

*T0, baseline:* After written informed consent, participants receive a personal link to the baseline questionnaire. Upon submission of this questionnaire participants are randomized as described below.

*Treatment:* The intervention group (IG) receives the intervention as described below. Those assigned to the waitlist-control group (WCG) will wait for five weeks before completing the first post-treatment assessment (T1.0). Subsequently, the same intervention as described above will be provided and an identical post-treatment assessment will be administered (T1.1) after the intervention. Participants in the WCG will be informed about this procedure immediately after randomization. For the sake of clarity the following nomenclature will be used subsequently: “treatment” describes the study phase between baseline and post-measurement and includes IG and WCG; “intervention” describes the Internet-based therapy that is conducted during treatment for IG and after the first post-treatment assessment for WCG.

*T1, post-treatment:* After completion of treatment, participants receive a link to the post-treatment questionnaire. The WCG receives an identical questionnaire again after completing the intervention.

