### Participants

#### Sample size and power calculation

Previous studies found effects of the Internet-based grief therapy of at least moderate size [46, 47]. Assuming moderate effect sizes, an alpha level of 0.05, and statistical power of 80% a target sample of 128 participants (64 for each group) is intended.

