### Measurements

The ICG [48] is used in its German version [55] to measure the primary outcome severity of PGD symptoms. It measures severity of PGD by assessing symptoms related to grief like yearning, intrusive thoughts, or resentment regarding the loss in 19 items which are rated by participants on a five-point Likert scale (never-always, 0–4) with regard to the last month. Three additional items were administered that are not included in the sum score but shall serve future comparability in the case of inclusion of PGD in ICD-11 as suggested by Maercker et al. [5]. They address feelings of guilt, difficulty accessing positive memories and anhedonia in questions adapted from Xiu et al. [56] as follows “I feel guilty about mistakes I made with regard to his/her death”, “It is really difficult for me to remember in detail happy moments with or images of him/her from the times before he/she died,” and “I no longer feel able to experience happiness, contentment, or joy since the loss of this person.”

Secondary outcomes, screening variables, moderators and mediators as well as used measures are summarized in Table 2.

**Table 2 Tab2:** Measurement tools

Construct	Instrument (abbreviation) [original and German source], additional information		Rating		Reliability	T-1	T0	Monitoring	T1-T4
		Item No.	Likert scale wording (scores)	Time frame					
Prolonged grief	Inventory of Complicated Grief (ICG) [48, 55], Cut-off^a^: ≥25 (sum score) [48]	19	never-always (0–4)	last month	*α*=.87, r_tt_ = .69 [55]	x	x		x
	Additional items [56], German version received from [name]	3	never-always (0–4)		–	x	x		x
	Prolonged Grief-13 – Interview version (IKT), [49, 61]	13	various formats (mostly 5-pointlLikert scales)	last month	–	x			
Depression	Patient Health Questionnaire (PHQ-9) [53, 62], Cut-off: ≥20 (sum, for severe depression) [63]	9	not at all-nearly every day (0–3)	last 2 weeks	*α*=.88 [64]	x	x	x	x
Posttraumatic stress	Impact of Event Scale-Revised (IES-R) [65, 66], Cut-off: > 0 (regression formula) [66], Screening: due to an event other than the loss, Baseline and post-assessments: due to loss	22	not at all-often (0,1,3,5)	last week	*α*=.71–.90, r_tt_ = .66–.80 [66]	x	x		x
Suicidal Ideation	Scale for Suicide Ideation (BSS or BSIS) [67, 68]	21	various formats (3 nuances each)	last week	*α*=.84–.89 [69]	x			

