Self-esteem	Rosenberg self-esteem scale [94, 95]	10	not at all true-completely true (0–3)	present	*α*=.72–.85 [95]		x		x
Self-efficacy	Skala zur Allgemeinen Selbstwirksamkeitserwartung (Self-Efficacy Scale, SWE) [96] (originally German)	10	not at all true-completely true (1–4)	present	*α*=.80–.90 [96]		x		x
Coping strategies	Brief COPE [97, 98]	28	not at all-a lot (1–4)	lifetime	*α*=.61–.81 [98]		x		x
Stigma	Grief Experience Questionnaire (GEQ), subscale Stigmatization [60], own translation	10	never-almost always (1–5)	since loss	*α*=.86 (English version) [60]		x		x
Working alliance	Working Alliance Inventory Short Form (WAI-S) [54, 99] (only Monitoring and T1)	12	never-always (1–7)	intervention	*α*=.81–.91 [99]			x	x
Mood	Self-Assessment Manikin (SAM) [52]	3	(1–9)	present	–			x	

^a^Where a cut-off value is provided, it is used at T-1 to determine whether a participant fulfils eligibility criteria

Abbreviations: *α*=Chronbach’s alpha (internal consistency); r_tt_ = test-retest reliability

Published German translations of measurement tools are used where available. For all other measurement tools [57–60], own translations were achieved as follows: the first authors translated the measurement tools from English to German. A native English speaker retranslated the result, which was then checked for accordance with the original tool. Any inconsistencies and challenges in translating, e.g., idioms, were discussed thoroughly within the research team.

In addition to the variables listed in Table 2, sociodemographic variables, current medical problems, drug and alcohol consumption, history of previous losses, traumatic experiences, and of psychological problems, and help-seeking behaviour are assessed at baseline (T0).

All measures except the Prolonged Grief Interview [49, 61] are assessed by online self-assessment questionnaires which minimizes potential assessment bias.

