### Statistical analysis

Demographic data and main outcomes will be reported using descriptive statistics. Chi-square and t-tests will be performed to examine whether randomization resulted in comparable groups and whether selective dropout occurred with regard to any pre-treatment characteristics.

To test the treatment effect, i.e. a significantly greater decrease in PGD and other mental health outcomes from baseline to post-treatment in the IG than in the WCG, a 2 × 2 repeated measure analyses of variance (ANOVA) will be conducted with time as the within-subject factor (baseline vs. post-treatment) and group as the between subject-factor (IG vs. WCG). Stability of treatment effects at 3, 6, and 12 month follow-up will be tested using two-tailed t-tests. Cohen’s d will be calculated to present effect sizes. Results will be shown for each outcome measure. Intention-to-treat analyses and completer analyses will be provided. Predictors of improvement in outcome measures and of dropout will be determined with linear and logistic regression analyses. To identify potential risk and protective factors for PGD severity and other bereavement outcomes as our secondary aim we will perform hierarchical regression analyses with baseline data, e.g., with religiousness, coping strategies, and attachment style as independent variables. All analyses will be conducted using SPSS, with an alpha level of 0.05.

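### The planned test leaves the second pre-randomisation ICG score (T-1) unused; adjusting for both T0 and T-1 would be more efficient, though T-1 itself may add little

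*Protocol article*

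**What the plan says.** All references are to the protocol article.

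- **Primary outcome (Methods, opening paragraph):** "Severity of PGD symptoms as measured with the Inventory of Complicated Grief (ICG) [48] is the main outcome".
- **Schedule (Measurements, Table 2):** the ICG row is marked at T-1, T0 and T1–T4. The PHQ-9 row is marked at T-1, T0, monitoring and T1–T4. The ICG row carries a cut-off of 25 or more and a test-retest reliability of .69.
- **Role of T-1:** footnote a to Table 2 says "Where a cut-off value is provided, it is used at T-1 to determine whether a participant fulfils eligibility criteria". Under Recruitment practices, "Interested persons can apply by submitting a screening questionnaire which determines whether they fulfil eligibility criteria". A T-1 ICG score therefore exists by design for everyone who is randomised.
- **Timing of T0 (Participant timeline):** "Upon submission of this questionnaire participants are randomized as described below". Both ICG scores therefore precede allocation.
- **Efficacy test (Statistical analysis):** a 2 × 2 repeated-measures ANOVA with "time as the within-subject factor (baseline vs. post-treatment) and group as the between subject-factor (IG vs. WCG"). T-1 does not appear in it.
- **Sample size:** 128 in total, 64 per group, for a moderate effect, alpha 0.05 and 80% power.

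**The concern.** A single ICG score with a test-retest reliability of .69 is a noisy measure of where a person started. The trial holds a second score on the same scale, taken before randomisation and complete by design, and uses it only as an eligibility gate. The article names the model, its factors and its two time levels, so this is a stated choice and not merely a detail left open.

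Two sources of precision are given up. A change-score comparison imposes a slope of 1 on baseline where ANCOVA would estimate it. The information that T-1 carries beyond T0 is also dropped. At stake are the width of the confidence interval for the treatment effect and, where T1 is missing, a complete predictor of the missing value.

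**Working it through.** **1. Reproduce the plan's figure.** Assume that moderate means d = 0.5, since the article gives no number. An exact two-sided two-sample t-test at alpha 0.05 needs 64 per arm, 128 in total, with power 0.801. The one-sided version needs 51 per arm and does not match. So 128 comes from an unadjusted comparison that takes no credit for any baseline correlation.

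**2. Residual variance, in units of the ICG variance.** Let a = corr(T0, T1), b = corr(T-1, T1), c = corr(T-1, T0).

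- Planned test (change from T0): 2(1 − a)
- ANCOVA on T0: 1 − a²
- ANCOVA on T0 and T-1: 1 − (a² + b² − 2abc)/(1 − c²). When a = b = c = r this is 1 − 2r²/(1 + r).

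**3. Every correlation equal to .69** (assumption: the Table 2 test-retest figure stands in for all three pairs).

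- Planned: 2 × 0.31 = 0.620
- ANCOVA on T0: 1 − 0.4761 = 0.524
- ANCOVA on both: 1 − 0.9522/1.69 = 0.437

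Replacing the change score with ANCOVA on T0 cuts the variance by 1 − 0.524/0.620 = 15.5%. Adding T-1 cuts it by a further 1 − 0.437/0.524 = 17%. Together the cut is 1 − 0.437/0.620 = 30%.

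**4. Increment from T-1 over ANCOVA on T0, other correlations.**

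| a (T0–T1) | b (T-1–T1) | c (T-1–T0) | ANCOVA T0 | ANCOVA both | Reduction |
|---|---|---|---|---|---|
| .69 | .69 | .69 | 0.524 | 0.437 | 17% |
| .50 | .50 | .69 | 0.750 | 0.704 | 6% |
| .69 | .60 | .69 | 0.524 | 0.495 | 5.6% |
| .69 | .69 | .85 | 0.524 | 0.485 | 7.4% |
| .50 | .50 | .85 | 0.750 | 0.730 | 2.7% |
| .69 | .60 | .85 | 0.524 | 0.523 | 0.1% |
| .69 | .476 | .69 (AR(1)) | 0.524 | 0.524 | 0% |

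With all three correlations equal, the reduction is 8% at .40, 11% at .50 and 14% at .60. It would reach 20% only at .80, above the documented figure.

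**5. Truncation.** T-1 is cut from below at 25. Simulating a cut-off between −1 and +1 SD of T-1, with all correlations .69 before selection, the increment from T-1 falls from 13% to 6%. The total reduction from the planned test to ANCOVA on both stays at about 29–30%.

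**6. Why a covariate and not an average.** Change from the mean of T-1 and T0 has variance 1 + (1 + c)/2 − (a + b). With all correlations .69 this is 0.465, 25% below the planned test. Under AR(1) it is 0.679, about 10% above it. A covariate cannot raise the large-sample variance; an average can.

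**7. Power at 64 per arm** (complete data, d = 0.5 on the raw ICG SD, normal approximation Φ(0.5√32/√v − 1.96), with v the residual variance).

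| Correlations | Planned | ANCOVA T0 | ANCOVA both |
|---|---|---|---|
| all .69 | 0.949 | 0.974 | 0.990 |
| a = b = .50, c = .69 | 0.807 | 0.904 | 0.921 |

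**The case against.** The strongest reply is that nothing here is an error. T0 is the last score before randomisation, taking it as the sole baseline is conventional, and the planned test is unbiased. Additional covariates are often settled in an analysis plan, which is not shown. The first part stands in full, and it makes this an efficiency point. The second has less force, because the article itself fixes the test and its two time levels.

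A reader might infer that the trial has no spare power and needs T-1 to rescue it. The documents do not support that. The sizing ignores baseline correlation. With the article's own .69, the planned test already has power of about .95 with complete data. With correlations of .50 to T1, where the planned test sits near 80%, most of the improvement comes from moving to ANCOVA on T0 (0.807 to 0.904), and T-1 adds under two points.

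A reader might also take 17% as the established gain, equivalent to 128/0.833, or about 154 participants. That is the favourable end. It applies one reliability coefficient, of unstated interval and population, to all three pairs. The ICG asks about the last month, so if T-1 and T0 lie close together their recall windows overlap and c may well exceed .69, which shrinks the increment.

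Finally, T-1 is an open application form completed before written consent. The article does not say whether its scores are linked to trial records or covered for outcome analysis. That is an open question, not evidence that they cannot be used.

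**Conclusion.** The point holds as a modest, low-cost improvement in efficiency. The planned ANOVA is valid, and 128 stands without the change. Adjusting for a score taken before randomisation does not bias the comparison; the cut-off at 25 applies to both arms alike and affects only the size of the gain.

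If all ICG correlations are .69, moving from the planned test to ANCOVA on both scores cuts residual variance by 30%, about half of it from ANCOVA on T0 alone. The part owed to T-1 is about 0–17% for correlations up to the documented .69. It is nil under AR(1) and 0.1–7.4% in the scenarios with T-1 and T0 correlated at .85. The size rests on assumed correlations; the direction does not, beyond the loss of one degree of freedom.

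**What to change.** Before the data are analysed, replace the time-by-group ANOVA for the primary comparison with an ANCOVA of T1 ICG on group, T0 ICG and T-1 ICG, or an equivalent constrained longitudinal model. For the waitlist group the T1 value is T1.0. Do the same for depression with the T0 and T-1 PHQ-9. Include both T-1 scores in the imputation model if one is used.

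Do not enter T-1 as a third ANOVA time level or as a plain average with T0. Do not extend the change to the IES-R: Table 2 shows that its T-1 version asks about an event other than the loss, so it is not a second baseline of the same quantity.

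The cost is a change of analysis wording, one degree of freedom for the added covariate, and confirmation that T-1 scores are linked to the trial record and may be used for outcome analysis. No new data are needed. If linkage cannot be confirmed, ANCOVA on T0 alone still delivers a substantial part of the gain.

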## Discussion

Family members of haematological cancer patients are highly burdened since they face high cancer-related distress which continues beyond bereavement. Their support needs often remain unmet. Easily available and accessible support is provided by Internet-based treatment programmes which were shown to have similar positive effects as face-to-face therapy, e.g., for depression [38]. To our knowledge there are no guided Internet-based therapies for bereaved individuals after the loss of a loved one due to haematological cancer. Our study aims at adapting and evaluating an Internet-based cognitive-behavioural grief therapy for this target group. Results of the study will provide information about the applicability and short- and long-term efficacy of the treatment regarding bereavement due to haematological cancer.

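### Two-tailed t-tests without a maintenance margin cannot show that effects are stable at 3, 6 and 12 months, and no untreated control remains by then

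*Protocol article*

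**What the plan says.** All statements are in the protocol article.

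- **Statistical analysis, follow-up:** "Stability of treatment effects at 3, 6, and 12 month follow-up will be tested using two-tailed t-tests". The section gives no margin, no confidence-interval criterion and no pair of means. On the error level: "All analyses will be conducted using SPSS, with an alpha level of 0.05".
- **Statistical analysis, treatment effect:** the only controlled comparison is a 2 × 2 repeated-measures ANOVA with "time as the within-subject factor (baseline vs. post-treatment) and group as the between subject-factor (IG vs. WCG". Intention-to-treat and completer analyses are both promised, and Cohen's d will be reported.
- **Participant timeline, Treatment:** "Those assigned to the waitlist-control group (WCG) will wait for five weeks before completing the first post-treatment assessment (T1.0". Then: "Subsequently, the same intervention as described above will be provided and an identical post-treatment assessment will be administered (T1.1) after the intervention".
- **Participant timeline, follow-up:** T2 to T4 come 3, 6 and 12 months after the intervention ends, in both groups.
- **Discussion:** "Results of the study will provide information about the applicability and short- and long-term efficacy of the treatment".

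**The concern.** A two-tailed t-test has no difference as its null hypothesis. It can give evidence of change, but a non-significant result is not evidence that change is absent or small. Stability is a claim of that second kind, and it needs a limit on how much deterioration would still count as stable. The plan sets none.

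The design adds a second limit. The untreated control period lasts five weeks and ends at T1.0. By T2 both arms have had the intervention, so the follow-up data hold no randomized untreated comparison. The wording on long-term efficacy suggests more than these data can give.

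At stake is the durability statement in the final report. The trial could describe effects as stable when a modest relapse has occurred, or could credit the intervention with 12-month improvement that has no comparator.

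**Working it through.** **1. The plan's own figure.** The sample-size section gives alpha 0.05, power 80%, a moderate effect and 128 participants (64 per group). No effect size is stated in numbers. Taking moderate as d = 0.5, the two-sided normal approximation gives 63 per arm (126), and the exact noncentral t gives power 79.5% with 63 per arm and 80.1% with 64. The figure reproduces. It is sized for a between-group difference of 0.5 SD, not for a stability question.

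**2. Where the follow-ups fall.** Order for the WCG: T0, five weeks' wait, T1.0, intervention, T1.1, then T2 to T4. Order for the IG: T0, intervention, T1, then T2 to T4. In both arms, T2 to T4 come after treatment.

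**3. The three possible contrasts.**

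| Contrast | What the t-test can show |
|---|---|
| End of intervention vs follow-up | Change since treatment ended; stability rests on non-rejection |
| Baseline vs follow-up | Whether scores still differ from baseline, without a control; the Background itself says that grief normally eases with time |
| IG vs WCG at follow-up | Difference between two treated groups; a null result is expected whether both hold their gains or both relapse |

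**4. Size under the first contrast.** Inputs assumed, because the article does not give them: true relapse 0.20 SD; equal SDs at both times; correlation ρ between end of intervention and follow-up of 0.50 or 0.69 (0.69 borrows the ICG test-retest value in Table 2); 20% loss for the pooled case, 128 × 0.80 ≈ 102 pairs.

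SD of the paired difference = √(2(1−ρ)): 1.000 at ρ = 0.50 and 0.787 at ρ = 0.69. Standardized change dz = 0.20 / SD of the difference: 0.200 and 0.254. The noncentrality is dz·√n, and the miss rate is 1 minus the power of the two-sided paired t-test at 0.05.

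| Pairs | ρ = 0.50: noncentrality, miss rate | ρ = 0.69: noncentrality, miss rate |
|---|---|---|
| 64 (one arm, no loss) | 1.60, 65% | 2.03, 48% |
| 45 (one arm, about 30% loss) | 1.34, 74% | 1.70, 62% |
| 102 (both arms, 20% loss) | 2.02, 48% | 2.57, 28% |

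**5. What a margin-based rule would deliver.** With 102 pairs, the 95% half-width is t × SD of the difference / √102: 0.196 SD (ρ = 0.50) and 0.155 SD (ρ = 0.69). With a margin of 0.25 SD, chosen only for illustration, and no true change, the chance that the interval excludes the margin is 71% and 89%. With 128 pairs it is 80% and 95%.

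The ordinary t-test on the same 102 pairs has the same 71% and 89% power to detect a 0.25 SD relapse. The margin rule therefore adds no precision. It moves the burden of proof: under it, loss of data makes stability harder to claim.

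**The case against.** The strongest reply is that the article never says a non-significant result will be read as maintenance. It names neither the contrast nor the decision rule, and a condensed article may leave both to a fuller document. If the contrast is baseline versus follow-up, significance would support persistence, and attrition would make that claim harder, not easier. This stands as a limit on wording: a reader might infer that the plan rewards dropout, but that holds only under the first contrast. It does not rescue the method, because the article does fix a test for stability and none of the three contrasts can carry that conclusion.

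Further points on this side also stand:

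- Uncontrolled follow-up is normal in a waitlist design and is not an error in itself. The timeline is open about it.
- A reader might infer that between-arm efficacy tests after T1 are planned. The ANOVA confines the group comparison to baseline and post-treatment.
- A reader might infer that only participants still responding are analysed. Intention-to-treat analyses are promised, and how missing data are handled is not shown.
- A reader might infer that treatment sought elsewhere during follow-up goes unrecorded. Measurements says that "help-seeking behaviour are assessed at baseline (T0"), but not that it is assessed at no other time.
- Cohen's d will be reported, so the observed size of change will be visible, though without a stated criterion for maintenance.
- One unpooled arm should not be set against a pooled remedy. Like for like, with 102 pairs, the miss rate for 0.20 SD is 28% to 48%.

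**Conclusion.** The point holds in a bounded form. Two-tailed t-tests without a margin cannot establish stability, and no follow-up contrast gives a controlled long-term effect. Under the natural reading, a 0.20 SD relapse would be missed in 48% to 65% of trials with 64 pairs and in 28% to 48% with 102 pooled pairs. These rates rest on the assumed relapse, correlation, equal SDs and 20% loss. The logical point does not depend on them.

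It would go too far to say that the plan declares effects stable whenever p exceeds 0.05, or that the trial's efficacy result is compromised. The randomized comparison from T0 to T1 and its sample size are untouched. This should be fixed, but it is not a condition for the trial's main conclusion.

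**What to change.** 1. In Statistical analysis, replace the follow-up t-tests by an estimate of mean ICG change from end of intervention (IG: T1; WCG: T1.1, not T1.0) to each of T2, T3 and T4, in both treated arms, with 95% confidence intervals. One mixed model using all available data is a suitable way, not the only one.
2. Fix a deterioration margin before follow-up data are examined, with its justification and the SD in which it is expressed. Baseline scores are truncated by the screening cut-off of 25, so baseline and post-treatment SDs may differ. Claim maintenance only if the interval excludes the margin.
3. Label T2 to T4 results as uncontrolled, and reword the Discussion from long-term efficacy to the course of symptoms after treatment.

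The cost is analysis wording and one margin to agree; no data collection changes. The downside is that stability becomes harder to claim: with 102 pairs, a 0.25 SD margin and no true change, the claim would succeed in 71% to 89% of trials. No reanalysis can restore an untreated comparison after T1.0.

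### The repeated-measures ANOVA gives the promised intention-to-treat analysis only with a missing-data method the article does not name, and neither intention-to-treat nor completer is said to decide efficacy

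*Protocol article*

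**What the plan says.** Under Methods, the article fixes one main outcome: "Severity of PGD symptoms as measured with the Inventory of Complicated Grief (ICG) [48] is the main outcome". Under Statistical analysis, the effect on this and the other mental health outcomes is tested by a 2 × 2 repeated-measures ANOVA "with time as the within-subject factor (baseline vs. post-treatment) and group as the between subject-factor (IG vs. WCG"). It is the only model given for the randomised T0–T1 comparison. The same section adds: "Intention-to-treat analyses and completer analyses will be provided", and "All analyses will be conducted using SPSS, with an alpha level of 0.05". It defines neither analysis set, ranks neither, and does not say how a missing T1 value enters the intention-to-treat analysis.

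Dropout is anticipated. Chi-square and t-tests will examine "whether selective dropout occurred with regard to any pre-treatment characteristics", and regression models will look for predictors of dropout. No dropout rate is given.

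Under Participant timeline, the waitlist group has its first post-treatment assessment after a fixed five weeks. The T1 link is otherwise sent once treatment is complete; the article does not say whether an intervention participant who stops early receives it.

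**The concern.** Two things the article fixes do not fit together. A repeated-measures ANOVA with two time points needs both values from each participant and excludes anyone lacking one. Everyone randomised has T0, because randomisation follows the baseline questionnaire, so it is T1 that decides who is analysed. An analysis of all randomised participants therefore needs something beyond the stated model.

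The second issue is rank. The ICG will be tested at 0.05 in both analyses. If one is significant and the other is not, the article does not say which decides efficacy.

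At stake is the main conclusion. T1 could be lost unequally: the intervention group works through ten writing tasks before T1, while the waitlist group waits five weeks and receives the intervention afterwards. If the loss is related to baseline severity or to response, the complete-case contrast is biased. The planned dropout tests and regressions would describe such loss, but they do not correct the effect estimate, and tests on baseline characteristics cannot reveal loss driven by response during treatment.

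**Working it through.** **Inputs from the article.** 128 participants, 64 per group; alpha 0.05; power 80%; a moderate effect; ICG test-retest reliability 0.69 (Table 2).

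**Assumptions.** Moderate means d = 0.5; tests are two-sided; 0.69 serves as the T0–T1 correlation ρ; all dropout rates and mechanisms.

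**1. The plan's own figure.** By the normal approximation, n per arm = 2(1.960 + 0.842)²/0.5² = 62.8, so 63. The noncentral t calculation gives 63.77, so 64 per arm and 128 in total, with power 80.1%. The stated target reproduces. It is a number of analysed participants, with no margin for missing T1.

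**2. Loss of T1 under that same calculation (equal in both arms).**

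| Assumed loss | Analysed per arm | Power |
|---|---|---|
| 10% | 64 × 0.9 = 57.6 | 75.8% |
| 20% | 64 × 0.8 = 51.2 | 70.7% |
| 30% | 64 × 0.7 = 44.8 | 64.8% |

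This is the two-sample calculation. For the time-by-group test with 51 per arm, power is 70.6% at ρ = 0.5 and 88.8% at ρ = 0.69, so the shortfall depends on the correlation.

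**3. Precision without dropout.** With two time points, the time-by-group test is a t-test on change.
- SD of change: √(2(1 − ρ)) = √0.62 = 0.787; standardised effect 0.5/0.787 = 0.635; power with 64 per arm 94.6%.
- Residual SD after baseline adjustment: √(1 − ρ²) = √0.5239 = 0.724; standardised effect 0.5/0.724 = 0.691.
- Variance ratio: (1 + ρ)/2 = 0.845.

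In simulation, power was 94% for the ANOVA and 97% for the baseline-adjusted model.

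**4. Dropout related to baseline, intervention group only, true effect 0.50 SD.** At about 21% dropout:
- listwise time-by-group test: 0.44 SD, power 84%;
- baseline-adjusted model: 0.50 SD, power 95%.

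Here the more severely affected dropped out more often. Were it the less severely affected, the ANOVA's bias would change sign.

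**5. Dropout related to change during treatment, intervention group only, no true effect.** The log-odds of dropout rise by 1 per SD of change for the worse.

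| Nominal dropout | Mean analysed of 64 (realised loss) | ANOVA bias | Type I error |
|---|---|---|---|
| 10% | 56.2 (12%) | −0.07 SD | 8% |
| 20% | 49.5 (23%) | −0.13 SD | 13% |
| 30% | 43.4 (32%) | −0.18 SD | 22% |

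With dropout completely at random, type I error stayed at about 5%.

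**6. Does the replacement cure response-related loss?** Suppose 20% of the intervention group lose T1 and gain nothing, while the rest gain 0.50 SD. The effect in all randomised is 0.8 × 0.50 + 0.2 × 0 = 0.40 SD. The listwise ANOVA gives 0.50, which is 0.50/0.40 = 1.25 times as large. Simulated, the common-baseline likelihood model also gave 0.50, as did regression imputation by arm with ANCOVA. With only T0 and T1, someone without T1 adds almost nothing to the T1 contrast. A delta adjustment does address this: worsening the imputed intervention-group values by 0.50 SD moves the estimate by 0.2 × 0.50 = 0.10, to 0.40.

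**The case against.** The strongest reply is that a condensed article leaves its missing-data method to a fuller plan that is not shown. That stands: the absence of an imputation method is not in itself an error. What remains is that the article commits to a particular model and a particular analysis set that do not match without such a method, and that it announces two analyses of the main outcome without ranking them.

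Three stronger readings are tempting, and the document does not support them.

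- *That the intention-to-treat result will simply be a completer result.* Imputation is not excluded, the ANOVA can be run on imputed data, and listing the two analyses side by side suggests they are meant to differ. Completer may also mean having finished the ten writing tasks, in which case the two sets could differ even without imputation.
- *That tests on baseline characteristics are the only safeguard against dropout.* The section also plans regressions on predictors of dropout, as well as the intention-to-treat analysis itself.
- *That a mixed model would remove the 25% overstatement in step 6.* It does not; it gives the same 0.50 SD. Baseline carried forward gave 0.40 in that scenario only because the scenario assumes no change in those who drop out, which is no general argument for single imputation.

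It is also fair to say that the article fixes one main outcome and one contrast, so the freedom left open is the analysis set and the handling of missing T1. That narrows the point but does not remove it.

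**Conclusion.** The point holds in this limited form. As written, the ANOVA delivers intention-to-treat only with an unnamed missing-data method, and the article does not say which of its two analyses decides efficacy. A baseline-adjusted model is better than the stated one on two counts: it is more precise even without dropout (94% against 97% power), and it remains unbiased when dropout depends on baseline (0.44 against 0.50 SD at about 21% dropout in the intervention group). These figures rest on d = 0.5, a correlation of 0.69 taken from test-retest reliability, and assumed dropout models. For loss related to unobserved response, neither the ANOVA nor its replacement is protected. The type I error of 8% to 22% in step 5 shows the possible scale for the complete-case ANOVA under one assumed mechanism; it is not a forecast for this trial.

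**What to change.** 1. Name intention-to-treat (all randomised, as allocated) as the primary analysis of the ICG at T1.
2. Define completer, by T1 data or by finished writing tasks, and label that analysis supportive.
3. Replace the ANOVA with a baseline-adjusted model: either SPSS MIXED on T0 and T1 with unstructured covariance, a common baseline mean and a group effect at T1, or ANCOVA on T1 after multiple imputation by arm.
4. Add a delta-adjusted sensitivity analysis that makes missing intervention-group values progressively worse, and report the delta at which the conclusion changes.
5. State whether intervention participants who stop early are sent the T1 questionnaire.

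The cost is analysis wording and a few extra runs in the same software. No change to the design or the questionnaires is needed.
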